## Abstract

**Background:**

The need to develop effective and accessible interventions for suicidal individuals engaging in heavy episodic drinking (HED) cannot be understated. While the link between alcohol use and suicidality is a complex one that remains to be elucidated, emotion dysregulation may play a key role in alcohol-related suicide risk in these individuals.

**Objective:**

In the current study, an 8-week Internet-delivered dialectical behavior therapy (DBT) skills training intervention was developed and preliminarily evaluated for suicidal individuals who engage in HED to regulate emotions. The aim of the study is to evaluate the feasibility and effectiveness of the therapist-assisted and Internet-delivered intervention, and to inform the design of a subsequent full-scale study.

**Methods:**

The study was a pilot randomized controlled trial comparing participants receiving immediate-treatment (n=30) to waitlist controls (n=29) over a period of 16 weeks. Intervention effects will be assessed longitudinally using hierarchical linear modeling and generalized estimating equations, along with analyses of effect sizes and clinically significant change. The primary outcomes are suicidal ideation, alcohol problems, and emotion dysregulation. Secondary outcomes include alcohol-related consequences, reasons for living, skills use, and depression.

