## Methods

This study is a pilot randomized controlled trial (RCT) comparing an Internet-delivered Dialectical Behavioral Therapy Skills Training (iDBT-ST) to a waitlist control condition. Participants were randomized to begin the 8-week intervention either immediately or after an 8-week waiting period. Assessments included monthly batteries, weekly surveys, brief daily reports, and acceptability questionnaires, all of which were all self-assessed. The project’s primary aim is to determine whether further revisions of the iDBT-ST intervention are needed, and to inform the design of a subsequent full-scale RCT.

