### Intervention

One primary aim of iDBT-ST is to replace maladaptive behavioral strategies with alternative strategies for coping and emotion regulation. The current intervention comprises the skill-training component alone, which is administered in a computerized format. The intervention was modified from an online DBT skills training intervention for emotion dysregulation [48].

Participants randomized into the iDBT-ST group were immediately enrolled into the online treatment program, and received weekly sessions over a period of 8 weeks. After completing the eighth session, participants in active treatment were transitioned into a follow-up phase that entailed monthly and weekly assessments without treatment. Participants randomized into the waitlist group received repeated monthly assessments as well as weekly surveys for 8 weeks prior to receiving treatment.

The iDBT-ST intervention was administered through an online electronic learning server (Articulate Online [49]) which consists of 8 sessions (Table 1) accessible through an access portal individualized for each participant, with one new session activated each week. The sessions begin with a weekly assessment, followed by (1) a review of the last session at weeks 2-8, (2) an introduction of the current session, (3) skills teaching, and (4) summary and consolidation. The skills were taught via videos and graphics describing the skills and examples, along with interactive activities. The intervention completion rate of each participant was also monitored through the server. If consented by participants, reminders to complete sessions were sent via their preferred method before the next session became available. Individualized assignments of skill practice were provided following the completion of each session. See Figure 1, Figure 2, and Figure 3 for screenshots of the intervention.

**Table 1 table1:** Description and function of session contents.

Session	DBT module	Skills	Function
1	Mindfulness	Observing, Describing, Participating	To introduce the foundational skills to develop nonjudgmental awareness of the present
2	Mindfulness	Nonjudgmentally, One-Mindfully, Effectively	To teach how to practice mindfulness with skillful effectiveness
3	Addiction	Dialectical Drinking, Clear Mind	To help learners find a middle path between oppressive sobriety and unrestrained freedom of drinking, and develop a clear mind

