### Analyses

Intervention effects will be evaluated by examining change outcomes as a function of treatment condition using both hierarchical linear modeling (HLM) [52] for outcomes with a normal distribution and generalized estimating equations (GEEs) [53,54] for count outcomes. Both HLM and GEEs accommodate observations that are missing at random, thus increasing the power of analyses. Analyses will be conducted using an intent-to-treat framework, in which all randomized and available participants will be included in the analyses. To examine changes over time for the entire sample, analyses will be conducted among all participants during all assessment waves (baseline to 16-week). A set of analyses will also be conducted using the first three assessment waves (baseline to 8-week) comparing immediate-treatment to no treatment, and at each condition’s relative pretreatment, midtreatment (4-week for iDBT-ST; 12-week for waitlist), and posttreatment (8-week for iDBT-ST; 16-week for waitlist) assessment phases.

Given the pilot nature of the study, all outcomes will be evaluated in terms of effect sizes as well as clinically significant change using Jacobson and Truax’s specifications [55]. Treatment effect sizes will be analyzed using Cohen’s *d* and Relative risk ratios for continuous and count outcomes, respectively. Cohen’s *d* will calculate within-condition effect sizes across all assessment waves. Descriptive analyses will also be conducted to examine acceptability.

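### The waitlist is an untreated control only to week 8, but the abstract frames a 16-week comparison and the plan does not say which of its three analysis sets gives the effect estimate

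*Protocol article*

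**What the plan says.** The abstract (Methods) presents the design as "comparing participants receiving immediate-treatment (n=30) to waitlist controls (n=29) over a period of 16 weeks".

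The body of the article gives the timing. Under Methods: "Participants were randomized to begin the 8-week intervention either immediately or after an 8-week waiting period". Under Intervention: "Participants randomized into the waitlist group received repeated monthly assessments as well as weekly surveys for 8 weeks prior to receiving treatment". The immediate arm, after its eighth session, is "transitioned into a follow-up phase that entailed monthly and weekly assessments without treatment".

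The Analyses section opens with a general statement: "Intervention effects will be evaluated by examining change outcomes as a function of treatment condition". It then sets out three analysis sets:

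- **Five waves.** To describe change in the sample as a whole, "analyses will be conducted among all participants during all assessment waves (baseline to 16-week".
- **Three waves.** Baseline to week 8, immediate treatment against no treatment.
- **Phase-aligned.** Each arm at its own "relative pretreatment, midtreatment (4-week for iDBT-ST; 12-week for waitlist), and posttreatment (8-week for iDBT-ST; 16-week for waitlist) assessment phases".

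The section does not say which set carries the conclusion on efficacy, and it does not give the form of time in the models. Cohen's d is defined within condition, across all waves.

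**The concern.** From week 8 the two arms exchange roles: the waitlist arm is treated and the immediate arm is in follow-up. A comparison described as running against waitlist controls for 16 weeks suggests a longer controlled period than the design provides.

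The larger difficulty is that three sets stand under one statement about intervention effects, and only one of them has a concurrent untreated control. If the phase-aligned results were read as the effect, any improvement that would have occurred anyway would be credited to treatment. That is a real possibility here. The Participants section selects people for recent suicidal ideation, recent heavy drinking episodes and emotion dysregulation one standard deviation above the norm, so some regression to the mean is to be expected. The results are meant to help decide whether larger studies are warranted, so a time-confounded estimate could mislead that decision.

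**Working it through.** The article gives no power, alpha, effect size or standard deviation, so there is no planned figure to reproduce. Its counts agree: 31 − 1 = 30 and 30 + 29 = 59.

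**Inputs from the article.** Assessments fall at weeks 0, 4, 8, 12 and 16. Treatment runs over weeks 0–8 in the immediate arm and weeks 8–16 in the waitlist arm.

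**Assumptions, not in the article.** The full 8-week effect is 1 unit of improvement (−1) and is the same in both arms. A share f is reached at mid-treatment. The immediate arm keeps shares m12 and m16 of the effect at weeks 12 and 16. There is no time trend unless stated.

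**1. Three-wave contrast.** Expected means are 0, −f, −1 (immediate) and 0, 0, 0 (waitlist). Centred times are −4, 0, 4, with sum of squares 32. The slope difference is −(4 × 1)/32 = −0.125 per week, which is −1.00 per 8 weeks. The full effect is recovered whatever f is.

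**2. Phase-aligned set.** Suppose there is no treatment effect and both arms improve by 0.4 per 8 weeks, so that expected means at weeks 0, 8 and 16 are 0, −0.4 and −0.8.

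- Immediate, pre to post: −0.4 − 0 = −0.4.
- Waitlist, pre to post: −0.8 − (−0.4) = −0.4.
- Concurrent difference at week 8: −0.4 − (−0.4) = 0.

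Both arms appear to respond to an inert treatment. If the whole 0.4 were instead regression to the mean in the first 8 weeks, with no change afterwards, the aligned changes would be −0.4 and 0. The arms would then differ although neither had benefited.

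**3. Five waves with condition by linear time.** The article does not specify this term. The calculation shows what it would do if it were chosen. Centred times are −8, −4, 0, 4, 8, with sum of squares 160.

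- Immediate slope = (4f − 4·m12 − 8·m16)/160 per week.
- Waitlist slope = −(4f + 8)/160 per week.
- Difference per 8 weeks = (8f + 8 − 4·m12 − 8·m16)/20.

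| f | m12 | m16 | Slope difference per 8 weeks |
|---|---|---|---|
| 0.50 | 1 | 1 | (4 + 8 − 4 − 8)/20 = 0 |
| 0.25 | 1 | 1 | (2 + 8 − 4 − 8)/20 = −0.10 |
| 0.75 | 1 | 1 | (6 + 8 − 4 − 8)/20 = +0.10 |
| 0.50 | 0.75 | 0.50 | (4 + 8 − 3 − 4)/20 = +0.25 |
| 0.50 | 0.50 | 0 | (4 + 8 − 2 − 0)/20 = +0.50 |
| 0.50 | 1.25 | 1.50 | (4 + 8 − 5 − 12)/20 = −0.25 |

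Over all scenarios tried, the term ran from −0.35 (f = 0.25 with further gain to 1.25 and 1.50) to +0.60 (f = 0.75 with full loss by week 16), against a true value of −1.00.

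In the first row the effect is not wholly lost from the model. The mean arm difference over the five waves is (0 − 0.5 − 1 − 0.5 + 0)/5 = −0.40, and it moves into the condition main effect. If the arms are constrained to a shared baseline, the interaction is −0.27.

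**4. Simulation of the first-row trajectory** (300 trials, 30 v 29, assumed effect 0.8 SD, within-person correlation 0.6, random-intercept model):

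| Model and term | Mean estimate | Rejected at 5% |
|---|---|---|
| Five waves, condition by linear time | 0.003 | 5.3% |
| Weeks 0–8, condition by linear time | −0.80 | 91.7% |
| Five waves, categorical week, week-8 contrast | −0.80 | 91.0% |

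Using five waves is therefore not harmful in itself. What matters is how time and exposure are coded.

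**The case against.** The strongest reply is that the authors already have the right comparison. The three-wave set is described as immediate treatment against no treatment, so they know that the untreated control ends at week 8. The five-wave set has a different stated purpose, change in the whole sample. The abstract is condensed: both arms were followed for 16 weeks, and the body states plainly when the waitlist arm starts treatment. The phase-aligned set gives its differing weeks openly and makes no claim of a concurrent control. Describing change in the comparison group is one of the study's aims. The trial is a pilot that disclaims a power analysis.

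Much of this stands, and it limits the point. A reader might infer that the plan cancels its own treatment effect, or that a 16-week condition effect must be null even when treatment works. The article does not support that. It specifies no linear condition-by-time term over five waves, and exact cancellation along the trajectories above needs particular values, the plainest being a linear, fully maintained gain of equal size in both arms. A reader might also infer that the three sets are given equal rank. The article states no ranking at all.

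What the reply does not answer is that all three sets follow a general sentence about intervention effects and none is named as the estimate. Nor does it supply a concurrent control for the phase-aligned set. Pilot status removes the power claim, but the need for a valid contrast remains.

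**Conclusion.** The point holds, with moderate severity. The controlled comparison lasts 8 weeks, the abstract's 16-week wording does not reflect that, and the Analyses section leaves open which set gives the intervention effect. The phase-aligned set is uncontrolled whatever model is used: its bias equals whatever change would have occurred without treatment (0.4 in the illustration, an assumed figure).

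The consequence for a five-wave linear interaction is conditional. It depends on a model the article does not state and on trajectories it does not give. Severity stops at moderate because the trial is a pilot, no power is claimed, and the valid baseline-to-week-8 contrast is already planned.

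**What to change.** 1. In Analyses, name the between-arm difference at week 8, from the baseline, 4-week and 8-week model, as the estimate of intervention effect, and report it with a between-arm effect size alongside the within-condition Cohen's d.
2. In the abstract, describe an 8-week controlled comparison with 16 weeks of follow-up.
3. Label the whole-sample five-wave results and the phase-aligned results as uncontrolled description.
4. If all five waves are used to estimate the effect, fit categorical study week with a time-varying treatment-exposure term (none, half or full course) instead of condition by linear time. State that this assumes the same effect in both periods. Coding the immediate arm as fully exposed after week 8 also assumes that its gain is kept.

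The cost is wording and, for item 4, one recoded variable. No new data are needed. The Results section says that the data are already under analysis, so the choice should be dated, with a statement of whether outcome results by arm had been seen.

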**Results:**

The trial is ongoing. A total of 60 individuals returned their informed consent and were randomized, of whom 59 individuals were intended to treat. A total of 50 participants in the study were retained through the 16-week enrollment.

**Conclusions:**

There is a dearth of evidence-based treatment for individuals presenting with high risk and complex behaviors. Furthermore, computerized interventions may provide a beneficial alternative to traditional therapies. The particular clinical features and treatment needs of suicidal individuals who also engage in HED constitute key domains for further investigation that are needed to consolidate the design of appropriate interventions for this high-risk population.

**Trial Registration:**

Clinicaltrials.gov NCT02932241; https://clinicaltrials.gov/ct2/show/NCT02932241 (Archived by WebCite at http://www.webcitation.org/6uJHdQsC2)

## Introduction

Suicide is the tenth leading cause of death across all age groups and is among the top four causes of death for Americans aged 10 to 54 years [1]. Furthermore, approximately 40% of suicides were found to be preceded by acute alcohol use [2]. Alcohol intoxication, both acute and chronic, has been identified as a uniquely salient risk factor for suicide among individuals with suicidal ideation [3-6]. These findings bring attention to the importance of attending to problematic alcohol use, and binge drinking in particular, in the management of suicide risk.

One possible explanation for the prevalence of suicide attempts preceded by binge drinking (ie, heavy episodic drinking; HED) is that suicidal heavy drinkers lack emotion regulation capabilities [7-10]. Emotion dysregulation is associated with risk for both suicide and problematic drinking [11-13]. Furthermore, suicide risk may be particularly elevated in individuals who engage in HED to reduce acute negative affect [9]. Given the behavioral complexity of suicidal individuals who drink alcohol to regulate emotions, an alcohol-focused treatment may not be sufficient to increase coping skills and/or distress tolerance techniques. This problem suggests the need for novel treatment approaches for HED and suicide that focus on increasing emotion regulation capabilities.

Dialectical behavior therapy (DBT) [14-16] is a behavioral intervention with strong empirical evidence in reducing suicidal behavior [17]. DBT was specifically designed for high risk, complex individuals, and consists of a combination of individual psychotherapy, group skills training, telephone coaching, and a therapist consultation team. Recent evidence has found that the DBT skill-training component alone is efficacious at reducing dysfunctional behaviors associated with emotion dysregulation [18,19], and that DBT skills usage mediates reductions in a variety of outcomes (including suicidal acts) [20]. Taken together, a DBT skills training intervention is a potent and efficient treatment package.

Unfortunately, despite the existence of evidence-based interventions such as DBT, there remains a vast discrepancy between the need and availability of treatment for suicidal individuals with cooccurring addictive disorders. For example, the majority of those who engage in suicidal behaviors never engage in treatment [1,21]. In addition, a rare study on alcohol-dependent suicide attempters who were hospitalized following a suicide attempt found that only 6% of participants had been enrolled in psychotherapy prior to hospitalization, and only 9% went on to receive psychotherapy in the month after discharge [22]. Interestingly, while severity of suicidal ideation has been associated with low endorsement of formal treatment engagement, suicidal individuals may be more apt to utilize such nontraditional modalities, including online and Web-based interventions [23]. For these individuals, technological mediation may offer a convenient and viable means to access needed treatment.

Technologically-assisted interventions for psychological disorders constitute the focus of a growing body of research [24-26]. Internet-delivered or computerized interventions are available to anyone with an Internet connection, and can be accessed at relatively low costs. Moreover, attitudinal barriers (eg, stigma associated with psychiatric diagnoses and attending face-to-face therapy) can be circumvented by treatment delivered anonymously in one’s home. However, although computerized interventions have shown preliminary promise in accessing and treating suicidal ideation [27,28], as well as strong evidence in reducing problematic alcohol use [29-30], they are rarely tested on high risk individuals presenting with complex and multiple disorders [31].

To address this treatment gap, an Internet-delivered DBT skills intervention targeting the underlying mechanism of emotion dysregulation was adapted for individuals who endorse suicidal thoughts and engage in HED. The current pilot study is a proof of concept study that seeks to evaluate the feasibility, acceptability, and preliminary efficacy of a DBT skills training intervention delivered via technology (ie, Web-based portal). The following aims are: (1) to determine the feasibility of recruiting clients, administering the treatment, and retaining clients in the treatment; (2) to evaluate the safety of the treatment with respect to potential adverse events; (3) to assess the feasibility of the research methodology (eg, reliability of the measures used, feasibility of random assignment to treatment, appropriateness of the control condition); and (4) to evaluate the feasibility of using a wait-list control group in this line of research, and changes over time among individuals in such a comparison group.

## Methods

This study is a pilot randomized controlled trial (RCT) comparing an Internet-delivered Dialectical Behavioral Therapy Skills Training (iDBT-ST) to a waitlist control condition. Participants were randomized to begin the 8-week intervention either immediately or after an 8-week waiting period. Assessments included monthly batteries, weekly surveys, brief daily reports, and acceptability questionnaires, all of which were all self-assessed. The project’s primary aim is to determine whether further revisions of the iDBT-ST intervention are needed, and to inform the design of a subsequent full-scale RCT.

### Participants

Participants were recruited from ads placed online (eg, Craigslist, Reddit) and in a local newspaper containing a brief description of the study. Interested participants were phone screened for eligibility on alcohol use severity, frequency of binge drinking episodes, suicidal ideation, emotion dysregulation, mental health treatment history, and demographic characteristics. Inclusion criteria included: (1) being 18 years or older, (2) endorsing suicidal ideation in the past month (defined as endorsing a wish to die at least once in the past 30 days), (3) engaging in at least two episodes of heavy drinking in the past month, (4) high emotion dysregulation (defined as scoring one standard deviation above the normative mean on the 16-item Difficulties in Emotion Regulation Scale [32]), and (5) residing in the United States. Exclusion criteria included: (1) currently receiving psychotherapy; (2) diagnosis of bipolar I, schizophrenia, or schizoaffective disorder; (3) non-English speaking; (4) unable to read or write; and (5) having no access to a computer connected to the Internet. Of 398 individuals who expressed initial interest, 60 of 91 eligible individuals returned the informed consent forms and were randomized into the immediate-treatment (n=31) and waitlist (n=29) groups. One person randomized to the immediate-treatment group did not complete any of the assessments, leaving 59 people included in the analyses. The phone screening process helped us prevent participants from enrolling with multiple identities.

### Ethics and Consent

The study has been approved by the Human Subjects Division of the Institutional Review Board at the University of Washington (IRB# 50295). Through the initial phone screening, all interested individuals were briefed on the aims of the study and their rights as participants. Participants were informed that their answers to the questions were voluntary, and that they could withdraw from the study at any time. Informed consent forms (see Multimedia Appendix 1) containing details about the study, procedures, and possible risks and benefits involved were provided to all eligible participants. Prior to randomization, participants were required to indicate on the consent forms their preferred mode of communication for receiving study materials, and to return their signed consent forms to the study site. Referral resources for treatment and crisis services were sent by email to interested callers who were deemed ineligible for the study. All participants consented to have their nonidentifiable data published. Access to the dataset is restricted to the principal investigator and authorized research assistants only. Complete data from this study can be obtained by contacting the first author once data analysis has been completed. iDBT-ST is not currently available online.

This study focuses on sensitive topics such as alcohol use and suicidal behavior, and the phone screen and outcome assessments contain questions that could potentially be distressing to participants. As a safety measure, participants were encouraged to consult with research staff whenever they felt distressed during screening and later participation. Suicide risk was also monitored and addressed in ways that are discussed later in this paper.

